#### 4.10 Secondary outcomes

Secondary outcomes include the following variables:

- Development of T2DM
- Fasting blood glucose
- Body weight
- Waist circumference
- Systolic blood pressure
- Physical activity level defined as the average daily MET (see definition in Section 3.7)
- Diet defined as the total 24-hour calorie intake (see definition in Section 3.8)

Development of T2DM will be analysed in the same way as the primary outcome, i.e. using survival analysis and Poisson regression as described in sections 4.9.2 and 4.9.3. No adjusted or subgroup analyses will be applied to this outcome except for a subgroup analysis according to baseline glycaemic status (normoglycaemia vs pre-diabetes).

##### 4.10.1 Descriptive analyses

Each continuous secondary outcome (i.e. all but development of T2DM) will be summarised by visit for each group and overall using mean, standard deviation, median and quartiles. Longitudinal plots will be used to display raw means and 95% confidence intervals by randomised group and by visit.

##### 4.10.2 Linear models

Repeated-measure generalised linear mixed models will be used to assess differences between groups over time for all continuous secondary outcomes. Models will include the randomised group, the visit and the group by visit interaction, use of insulin during pregnancy and the baseline value of the outcome as fixed effects. Random intercepts by subject and by study centre will be added to the model. Within-subject correlations as well as within-site correlations will be assumed to follow an exchangeable structure.

The effect of the intervention will be estimated as the adjusted mean difference at each visit and overall (all visits combined) together with its 95% confidence interval. A p-value from the likelihood ratio test will only be calculated for the overall difference based on all visits combined.

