| Healthcare utilisation (hospital, clinics, tests, medications) |                |   | X | X               | X              | X              |
| Serious Adverse Events #                            |                |   | X | X               | X              | X              |

\*OGTT will not be performed if interim diagnosis of T2DM is adequately confirmed by appropriate source documents

^HbA1c from old records (if available)

\$ If HbA1c is  $\geq 6.5\%$ , then an OGTT will be performed.

\*\* Modified Global Physical Activity Questionnaire and Intake 24 Diet recall

# to be filled only when severe adverse event is seen any time after randomisation

From March 25, 2020, due to lockdown measures relating to the Covid-19 emergency, the following changes to participant follow-up have been instituted:

1. All follow-up visits with study participants will be conducted remotely via telephone. This will exclude the ability to collect any data relating to anthropometric measurements, OGTT, HbA1c and vitals (BP and heart rate).
2. All participants who have completed at least 12 months follow-up (and, if randomised to the intervention, have completed all aspects of the intervention) will have an EOS visit scheduled as their next visit.
3. Once lockdown conditions have been lifted, all participants will be scheduled for a visit to, at a minimum, undergo testing for HbA1c and undergo an OGTT. If conditions allow, in-clinic visits will be arranged for anthropometric measures and vitals (BP and heart rate).

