#### 3.5 Early study discontinuation/Lost to Follow-up

Early termination is captured on the CRF and may be due to one of the following reasons:

- Withdrawal of Informed consent for follow-up visits
- Development of T2DM
- Occurrence of pregnancy
- Unable to contact or unable to follow-up

In case of early termination, a patient was expected to have an EOS visit completed at the time of termination. For those who did not terminate early, EOS visits with at least partial data collection were to be conducted after 1 July 2020.

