### 4.1 General Principles

Analyses will be performed using SAS Enterprise Guide version 8.3 or higher (SAS Institute Inc., Cary, NC, USA).

All variables will be analysed by descriptive statistical methods. The number of data available and missing data, mean, standard deviation, minimum, quartiles, median, and maximum will be calculated for continuous data. Frequency tables will be generated for categorical data. For categorical variables, the number and percentage of patients with a specific level of the variable will be presented.

All tests will be two-sided with a type-I error rate of 5%. Analyses of the primary outcome (change in category of glycaemia from normoglycaemia to IGT, IFG or T2DM or from IFG or IGT to T2DM) will be unadjusted for multiplicity; however, we will control the family-wise error rate across secondary outcomes using a Holm-Bonferroni correction [2]. No other multiplicity adjustment will be applied.

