### 4.4 Baseline characteristics

The following variables will be summarized at baseline:

- Socio-demographic characteristics
  - Age
  - Primary language
  - Country
  - Religion
  - Highest educational qualification (3 categories will be created: up to primary including none, secondary and other higher degree (diploma/undergraduate and graduate)
  - Years of schooling

- Current employment status
  - Current employment classification
  - Average household size of participant
- Risk Factors:
  - Reproductive history (Gravida, livebirths, time since delivery)
  - Family history
  - Obstetric history
  - Medical history (including history of hypertension and usage of hypertension medication)
  - Time since detection of GDM
  - Alcohol consumption
  - Tobacco consumption
- Vital Signs and anthropometric measures at baseline:
  - Height
  - Weight
  - Waist circumference
  - Waist circumference > 80 cm will be used to create a categorical variable separately
  - Hip circumference
  - Waist/Hip ratio
  - BMI
  - Blood pressure
  - Hypertension at baseline defined by SPB $\geq$ 140 and DBP $\geq$ 90
  - Heart rate
- Other Factors:
  - Use of insulin and pharmacotherapy during index pregnancy
  - Diet
  - Metabolic equivalent of task (MET) information at baseline(minutes/week)

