#### **4.9.4 Adjusted analyses**

Both the Cox and Poisson models will be repeated after adding the following covariates to the model: prediabetes (yes/on), BMI (underweight, normal, overweight, obese), time since GDM-affected pregnancy (as a continuous variable, measured in months) and age (as a continuous variable, measured in years).

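### The mixed models for the six continuous secondary outcomes leave out time since delivery, a recorded baseline variable, so a little precision goes unused (minor)

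*Combined protocol and SAP*

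**What the plan says.** SAP 4.10.2 names every term in the models. The fixed effects are randomised group, visit, the "group by visit interaction, use of insulin during pregnancy and the baseline value of the outcome as fixed effects". On the random side, "Random intercepts by subject and by study centre will be added to the model". The notes under Tables 9 and 10 repeat this list. No adjusted version is planned for the continuous outcomes.

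Time since delivery appears elsewhere in the SAP:

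- SAP 4.4 lists it for the baseline table: "Reproductive history (Gravida, livebirths, time since delivery"). Table 3 has a row for it.
- SAP 4.9.4 adds it to the adjusted Cox and Poisson models for the primary outcome: "time since GDM-affected pregnancy (as a continuous variable, measured in months").
- SAP 4.9.5 uses it, split at the median, as a subgroup factor.

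The entry window is set by the eligibility OGTT, at 3 to 18 months post-partum (Protocol 3.2, SAP 2.3.1). Protocol 5.1.2 allows randomisation on the same day but does not require it, so some women may be beyond 18 months at randomisation.

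**The concern.** Body weight and waist may still be changing in the months after childbirth. A woman measured at 3 months and another measured at 18 months can share a baseline weight yet have different expected weights one or two years on. The outcome's own baseline cannot separate them. Time since delivery can, and the SAP already treats it as relevant to glycaemic outcome.

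Left out, whatever variance it explains stays in the error term. The continuous outcomes are tested within a Holm family (SAP 4.1), so their precision has some value. In a linear model, adding a pre-randomisation covariate leaves the target mean difference unchanged and affects only its standard error. In a Cox model, adding a prognostic covariate changes the hazard ratio being estimated. The SAP therefore plans the adjustment where it alters the quantity estimated and omits it where it would not.

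**Working it through.** **1. The plan's own figure.** Body weight is the only continuous outcome with a power statement (Protocol 1.5): 1414 women, 90% power, 1.80 kg, SD 10.4. SAP 4.1 states: "All tests will be two-sided with a type-I error rate of 5"%.

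- n per arm = 2(1.960 + 1.282)² × 10.4² / 1.80² = 702, or 1404 in total. The 1414 is reproduced, with no dropout allowed for.
- Power at 707 per arm is 90.2%. With 20% lost (about 566 per arm), the difference detectable with 90% power is 3.242 × 10.4 × √(2/566) = 2.00 kg.

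These figures use 5% without the Holm step.

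**2. What the planned baseline adjustment gains.** The residual SD is 10.4 × √(1 − r²), where r is the correlation between baseline and follow-up weight. The documents do not give r. With 20% lost, the detectable difference falls from 2.00 kg to 1.43, 1.20 and 0.87 kg at assumed r of 0.7, 0.8 and 0.9.

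**3. How much time since delivery might explain, first route.** All inputs are assumptions: entry uniform on 3 to 18 months; exponential post-partum decline with time constant τ of 6 or 12 months; mean loss L between months 3 and 18 of 3 kg (1.5 to 4.5); residual SD of 5 kg (4 to 6).

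- Expected further loss over m months from entry at month t is A·e^(−t/τ)·(1 − e^(−m/τ)), with A = L / (e^(−3/τ) − e^(−18/τ)).
- Partial R² = SD² / (SD² + residual SD²), where SD is the spread of that expected loss across women.
- Central case (L = 3, residual SD 5): SD is 0.54 kg (τ = 12, m = 12) to 0.81 kg (τ = 6, m = 24), so R² is 1.2% to 2.6%.
- Low corner: 0.27² / (0.27² + 6²) = 0.2%.
- High corner: 1.216² / (1.216² + 4²) = 8.5%.

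**4. Second route.** Assume a linear slope b given baseline weight, and r = 0.9. The SD of a uniform variable on 3 to 18 is 15/√12 = 4.33 months, with variance 18.75. The residual variance is 10.4² × 0.19 = 20.55. R² = 18.75b² / 20.55 gives 0.9%, 3.6% and 8.2% at b = 0.1, 0.2 and 0.3 kg per month. The two routes cover much the same range.

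**5. Effect on precision.** The standard error is multiplied by √(1 − R²). The gain in equivalent sample size is 1/(1 − R²) − 1.

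| Partial R² | SE cut | Equivalent extra women |
|---|---|---|
| 0.2% | 0.1% | 0.2% (3 of 1414) |
| 1% | 0.5% | 1.0% (14) |
| 3% | 1.5% | 3.1% (44) |
| 8.5% | 4.3% | 9.3% (131) |

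At r = 0.9 with 20% lost, the detectable weight difference moves from 0.874 kg to 0.870 kg (R² 1%) or 0.861 kg (R² 3%).

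**6. Simulated check.** ANCOVA at one follow-up, n = 1131 (1414 × 0.8), r = 0.9. With b = 0.1, adding time since delivery took the mean standard error from 0.272 to 0.271. With b = 0.2 it went from 0.276 to 0.271. The average treatment estimate did not move. These are single-visit approximations to the repeated-measures model.

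**The case against.** The strongest defence is that 4.10.2 follows the SAP's own pattern. The main Cox model for the primary outcome (SAP 4.9.2) also omits time since delivery; it contains group, insulin use and site. The adjustment in 4.9.4 is a supplementary re-run. The main model in 4.10.2 is already fuller than the primary's, because it adds the outcome's baseline. On that view the only gap is a missing supplementary run, and filling it is a matter of preference. The size is also small and wholly assumed, and it is worked out for weight alone; nothing in the documents supports a figure for fasting glucose, blood pressure, activity or calories.

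Most of this stands, and it is why the point is minor. It does not justify the omission: no reason is given, and the variable is recorded. A supplementary run matching 4.9.4 would restore consistency but would leave the tested result as it is.

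A reader might go further and ask for a lockdown term in the same models. One visit label can mix records from before and after March 2020, since for women who did not stop early "EOS visits with at least partial data collection were to be conducted after 1 July 2020" and SAP 3.4 reallocates those visits to planned months. The documents do not support lockdown as a precision covariate, for three reasons:

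- It is post-randomisation. No such variable is listed, so it would have to be derived from visit dates, and no end date is given.
- The notes to Protocol Table 3 say "All follow-up visits with study participants will be conducted remotely via telephone", which ruled out weight, waist, blood pressure and OGTT at those contacts. Only diet and activity could carry a telephone effect.
- The same notes set an extra condition on early EOS scheduling for the intervention arm (completion of the intervention), so timing can depend on allocation. If the share of later records differed by 10 points between arms, an assumed shift of 1 to 2 kg would move the estimate by 0.10 × 1 to 0.10 × 2 = 0.1 to 0.2 kg. That raises a question about what is being estimated; it is not free precision.

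**Conclusion.** The point holds as a minor improvement. For weight, the likely cut in standard error of 0.5 to 1.5% rests on an assumed partial R² of 1 to 3%. The upper end, about 4%, needs the most favourable corner of every assumption together. Waist may behave similarly, but no figure is offered for it or for the other four outcomes.

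Two stronger inferences are not supported. A reader might take the omission as a source of bias. It is not, because leaving out a prognostic baseline variable does not bias a randomised linear comparison. A reader might also extend the point to every secondary outcome. Development of T2DM is in the same Holm family, but it is analysed with the Cox and Poisson models (SAP 4.10) and is untouched by 4.10.2.

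**What to change.** In SAP 4.10.2, add time since delivery at randomisation, continuous and in months, as a fixed effect. Make the same change in the notes to Tables 9 and 10. The cost is one degree of freedom per model and a line of wording; no new data are needed.

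Keep any lockdown indicator out of the main model. If the period is to be examined, use records dated on or after 25 March 2020 to define a separate sensitivity analysis, and state that such records include both telephone contacts and later clinic visits.

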#### 3.4 Handling of last (EOS) visit

Given study participants entered the study at different times and were followed for various durations, the End of Study (EOS) visit will occur at different times for different participants.

For longitudinal analyses and descriptive analyses by visit, EOS visits will be re-allocated according to the planned visit schedule (i.e. Month 1, 6, 12, 18, 24 or 30). The allocation, based on the number of days between the date of randomisation and the EOS visit, will be done as follows:

- Month 6: number of days between 93 and 273 (inclusive)
- Month 12: number of days between 274 and 456 (inclusive)
- Month 18: number of days between 457 and 638 (inclusive)
- Month 24: number of days between 639 and 821 (inclusive)
- Month 30: number of days between 822 and 1003 (inclusive)
- Month 36: number of days between 1004 and 1186 (inclusive)

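### One constant within-woman correlation and variance from month 6 to month 36, with staggered follow-up, can make late-visit intervals too narrow and, depending on how the overall difference is defined, inflate its test

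*Combined protocol and SAP*

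**What the plan says.** SAP 4.10.2 fits one repeated-measures model to each continuous secondary outcome. The fixed effects are arm, visit, arm by visit, insulin use in pregnancy and the baseline value, with no baseline-by-visit term. On the covariance it says "Random intercepts by subject and by study centre will be added to the model" and "Within-subject correlations as well as within-site correlations will be assumed to follow an exchangeable structure". The notes to Tables 9 and 10 repeat both sentences.

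The reported effect is the "adjusted mean difference at each visit and overall (all visits combined) together with its 95% confidence interval". On testing: "A p-value from the likelihood ratio test will only be calculated for the overall difference based on all visits combined". The SAP does not define how visits are weighted in that overall difference.

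SAP 3.4 notes that "study participants entered the study at different times and were followed for various durations" and re-allocates end-of-study visits to windows up to month 36. SAP 2.2 sets a 12-month minimum. SAP 4.1 sets a two-sided 5% level and adds that "we will control the family-wise error rate across secondary outcomes using a Holm-Bonferroni correction". Six of the seven secondary outcomes come from this model.

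No within-woman correlation is given for any outcome. No robust standard error, random slope or covariance sensitivity analysis is specified.

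**The concern.** An exchangeable structure says that a woman's month-6 value predicts her month-36 value as well as her month-30 value does, and that residual spread is the same at every visit. Measures that track over years usually behave otherwise. Once the baseline value is in the model, a correlation with baseline that falls over time makes residual variance rise from month 6 to month 36. Protocol 3.3.1 expects about 30% of participants to need more intensive support, with weight gain by month 6 as the trigger. That fits diverging weight paths, though it does not quantify them.

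Staggered follow-up makes the assumption matter more. Women with short follow-up contribute to late-visit estimates only through the assumed covariance. The Covid-19 changes in protocol section 5.1 (remote visits without anthropometry, blood pressure or blood tests; early end-of-study scheduling for many) may thin the late data further.

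At stake are the month-by-month intervals in Tables 9 and 10, especially the late ones that a reader would use to judge whether an effect lasts, and possibly the level of the overall tests that enter the Holm procedure.

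**Working it through.** **Inputs from the documents.** 1:1 allocation; 1414 women; 12-month minimum; visits at months 6 to 36; 5% two-sided; body-weight SD 10.4 kg (protocol synopsis).

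**Assumptions, because the documents give no figures.** The true covariance is varied in the table below. In the base case last visits fall evenly on months 12, 18, 24, 30 and 36, so 100, 100, 80, 60, 40 and 20% of women are seen at months 6 to 36. Centre and insulin effects are left out.

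**Method.** Let p_k be the share of women with k visits, W_k the best-fitting exchangeable covariance (maximum likelihood, large sample) and V_k the true covariance after baseline adjustment.
- A = Σ p_k W_k⁻¹ and B = Σ p_k W_k⁻¹ V_k W_k⁻¹.
- The variance the model reports is proportional to A⁻¹; the true variance is proportional to A⁻¹BA⁻¹. The factor 4/N cancels.
- For a contrast c, r = √[c′A⁻¹c / c′A⁻¹BA⁻¹c], and the actual error rate is 2·[1 − Φ(1.96·r)].

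**The plan's own figure first.** If the truth is exchangeable, r = 1 and the rate is 5.0% for every contrast, as SAP 4.1 states.

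**Other truths.** AR(1) values are per 6 months. Slope SDs are in baseline SDs per year: 0.1 × 10.4 = 1.04 kg and 0.2 × 10.4 = 2.08 kg per year.

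| True covariance | Correlation with baseline, M6 → M36 | Overall, equal weights: r, rate | Overall, observed-visit weights | M6 CI misses | M36: r, CI misses |
|---|---|---|---|---|---|
| Exchangeable 0.9 | 0.90 → 0.90 | 1.00, 5.0% | 5.0% | 5.0% | 1.00, 5.0% |
| AR(1) 0.90 | 0.90 → 0.53 | 0.817, 11.0% | 6.1% | 0.6% | 0.696, 17.2% |
| AR(1) 0.95 | 0.95 → 0.74 | 0.800, 11.7% | 6.2% | 0.3% | 0.671, 18.8% |
| AR(1) 0.98 | 0.98 → 0.89 | 0.791, 12.1% | 6.3% | 0.2% | 0.656, 19.9% |
| Random slope 0.1 | 0.96 → 0.92 | 0.877, 8.5% | 5.6% | 2.9% | 0.799, 11.7% |
| Random slope 0.2 | 0.96 → 0.83 | 0.773, 13.0% | 6.4% | 0.7% | 0.636, 21.3% |
| 0.5 constant + 0.35 AR(1) 0.8 + 0.15 noise | 0.78 → 0.59 | 0.909, 7.5% | 5.4% | 2.7% | 0.852, 9.5% |
| Noisy: 0.3 constant + 0.3 decaying (24-month scale) + 0.4 noise | 0.53 → 0.37 | 0.956, 6.1% | 5.2% | 4.0% | 0.930, 6.8% |

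Example: AR(1) 0.90 at month 36 gives 1.96 × 0.696 = 1.364, and 2·[1 − Φ(1.364)] = 17.2%.

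**Role of staggering.** With everyone followed to month 36, the equal-weight overall rate is 5.0% in every row, but the month-36 interval for AR(1) 0.90 still misses 10.7% (r = 0.823). If last visits fall 30, 30, 20, 15 and 5% on months 12 to 36, the equal-weight rate for AR(1) 0.90 rises to 16.2% (r = 0.713).

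**Simulation check** (600 trials of 1414 women, actual likelihood-ratio tests, AR(1) 0.90). Equal weights rejected 10.8%, observed-visit weights 5.7%, a single arm effect without interaction 4.5%; the month-36 interval missed 16.2%. Across the four non-exchangeable covariances simulated, the equal-weight test at the first Holm step (0.05/7 = 0.7%) rejected 1.3–2.3%.

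**With an unstructured covariance** (200 trials per scenario, Monte Carlo error about 1.5 points), the equal-weight test rejected 1.5–6.5% and the month-36 interval missed 2–6%, both consistent with 5%. In a separate simulation (800 trials per covariance, correlation with baseline falling from 0.93–0.95 to 0.76–0.87), robust standard errors brought the equal-weight test to 4.6–5.8%.

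**The case against.** A reader might infer that the secondary tests reject about twice as often as the stated 5%. The documents do not support that as a statement about the plan.

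- **The contrast is undefined.** A doubling needs equal visit weights, which give sparse month 36 as much weight as month 6. Observed-visit weights, or a single arm effect, keep the rate at about 5–6%. This stands. It does not clear the plan: a model with an arm-by-visit term and an overall adjusted mean per arm in Table 9 can equally be read as an equal-weight average.
- **The correlations and late-visit numbers are not given.** This stands. Every figure other than the 5.0% is conditional on assumptions.
- **Weight is not every outcome.** This stands. For noisy measures such as METs or diet recall the rate is about 5–6.5%. Fasting glucose comes mainly from the OGTTs at months 12, 24 and 36 (protocol 5.1.4), so a six-visit layout does not represent it.
- **Late-visit intervals carry no p-value.** True, but they are reported as 95% intervals, and their undercoverage does not depend on how the overall difference is defined.

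**Conclusion.** The concern holds in conditional form. The SAP fixes an exchangeable within-woman structure over three years of staggered visits without any protection. If correlation decays or variance grows, month-36 intervals are too narrow (missing about 11–21% under weight-like assumptions) and month-6 intervals too wide. The overall test then rejects about 8–12% with equal visit weights (13% in the most extreme slope case, more with sparse late visits) and about 5–6% with observed-visit weights. For noisy outcomes the effect is small.

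The size rests on assumed correlations and an assumed spread of follow-up; the direction of the interval errors was the same in every non-exchangeable case tried. Only secondary and other continuous outcomes are affected, not the primary Cox analysis. It is worth correcting because the change is small and standard for about 1,400 women and six visits.

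**What to change.** In SAP 4.10.2 and the notes to Tables 9 and 10:

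1. Replace the exchangeable within-subject sentence with an unstructured covariance across visits (subject = participant). Keep the random centre intercept and drop the subject intercept, which is then redundant.
2. Pre-specify a fallback on non-convergence: heterogeneous Toeplitz, then the random-intercept model with empirical (sandwich) standard errors. State the clustering unit, since centre is also a random effect and SAP 2.3 lists only 20 sites.
3. State the visit weights that define the overall difference.
4. Test that contrast in the same model: either a Kenward-Roger Wald/F test in place of the likelihood-ratio test, or a likelihood-ratio test of the same contrast under maximum likelihood.
5. State that one record per woman per visit window is used after end-of-study re-allocation, and which record is kept if two fall in one window.

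The cost is SAP wording and code, with no change to data collection. The downsides are more covariance parameters, a possible fallback and somewhat wider late-visit intervals.
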